| The laboratories for   | The live virus neutralizing antibody measure is by Jiangsu Provincial Center                                                                                                                                                                                                                                                                                                                                                                                                                                                                                                                                                                                                                                                                                                                                                                                                                                                                                                                                                                                                                                                                                                                                                                                                                                                                                                                                |

|         |                                                                                                                                                                                                  |
|---------|--------------------------------------------------------------------------------------------------------------------------------------------------------------------------------------------------|
| testing | for Diseases Control and Prevention

Test for antibody level measured by ELISA, pseudoviruses neutralize antibodies, B cell, T cell subgroups and germ lines is by Vazyme Biotech Co., Ltd |
|---------|--------------------------------------------------------------------------------------------------------------------------------------------------------------------------------------------------|

Table 1. “0-28 days” regimen subjects visit plan

| Visit No.                                          | V0*     | V1        | V2         | V3         | V4          | V5        | V6         | V7         | V8          |
|----------------------------------------------------|---------|-----------|------------|------------|-------------|-----------|------------|------------|-------------|
| Day/Month                                          | Day 28  | Day 35    | Day 42     | Day 56     | Day 150     | Day 157   | Day 164    | Day 178    | Day 330     |
| Visit interval                                     | V0      | V0+7 days | V0+14 days | V0+28 days | V0+4 months | V4+7 days | V4+14 days | V0+28 days | V4+6 months |
| Time window                                        | ±3 days | +3 days   | +3 days    | +3 days    | +7 days     | +3 days   | +3 days    | +3 days    | ±15 days    |
| Informed consent                                   | ●       |           |            |            | ●           |           |            |            |             |
| Demographic information collection                 | ●       |           |            |            |             |           |            |            |             |
| Physical examination and preliminary screening     | ●       |           |            |            | ●           |           |            |            |             |
| Randomization                                      | ●       |           |            |            |             |           |            |            |             |
| Blood collection                                   | ●(20ml) |           | ●(10ml)    | ●(20ml)    |             |           | ●(20ml)    |            | ●(10ml)     |
| Observation for 30 min post-vaccination            | ●       |           |            |            | ●           |           |            |            |             |
| Safety visit(AR/AE)                                | ●       | ●         | ●          | ●          | ●           | ●         | ●          | ●          | ●           |
| Report serious adverse event(SAE)※                 | ●       | ●         | ●          | ●          | ●           | ●         | ●          | ●          | ●           |
| Distribution of diary card                         | ●       |           |            |            | ●           |           |            |            |             |
| Return of diary card and distribute a contact card |         | ●         |            |            |             | ●         |            |            |             |
| Return of contact card                             |         |           |            | ●          |             |           |            | ●          |             |
| Record on the Vaccination                          | ●       | ●         | ●          | ●          | ●           | ●         | ●          | ●          | ●           |

|                                     |   |   |   |   |   |   |   |   |   |
|-------------------------------------|---|---|---|---|---|---|---|---|---|
| and Visit Record Form               |   |   |   |   |   |   |   |   |   |
| Record the combination drug/vaccine | • | • | • | • | • | • | • | • | • |

\* V0 is the time for the enrollment for a booster dose

Table 2. “0-56 day” regimen subjects visit plan

| Visit No.                                          | V-1     | V0*     | V1            | V2             | V3             | V4              | V5        | V6             | V7             | V8              |
|----------------------------------------------------|---------|---------|---------------|----------------|----------------|-----------------|-----------|----------------|----------------|-----------------|
| Day/Month                                          | Day 28  | Day 56  | Day 63        | Day 70         | Day 84         | Day 180         | Day 187   | Day 194        | Day 208        | Day 360         |
| Visit interval                                     | V-1     | V0      | V0+
7 days | V0+
14 days | V0+
28 days | V0+
4 months | V4+7 days | V4+
14 days | V0+
28 days | V4+
6 months |
| Time window                                        | 0       | ±3 days | +3 days       | +3 days        | +3 days        | +7 days         | +3 days   | +3 days        | +3 days        | ±15 days        |
| Informed consent                                   | •       |         |               |                |                | •               |           |                |                |                 |
| Demographic information collection                 | •       |         |               |                |                |                 |           |                |                |                 |
| Physical examination and preliminary screening     | •       | •       |               |                |                | •               |           |                |                |                 |
| Randomization                                      |         | •       |               |                |                |                 |           |                |                |                 |
| Blood collection                                   | •(20ml) | •(10ml) |               | •(10ml)        | •(20ml)        |                 |           | •(20ml)        |                | •(10ml)         |
| Observation for 30 min post-vaccination            |         | •       |               |                |                | •               |           |                |                |                 |
| Safety visit(AR/AE)                                |         | •       | •             | •              | •              | •               | •         | •              | •              | •               |
| Report serious adverse event(SAE)※                 |         | •       | •             | •              | •              | •               | •         | •              | •              | •               |
| Distribution of diary card                         |         | •       |               |                |                | •               |           |                |                |                 |
| Return of diary card and distribute a contact card |         |         | •             |                |                |                 | •         |                |                |                 |

|                                                    |   |   |   |   |   |   |   |   |   |   |
|----------------------------------------------------|---|---|---|---|---|---|---|---|---|---|
| Return of contact card                             |   |   |   |   | • |   |   |   | • |   |
| Record on the Vaccination
and Visit Record Form | • | • | • | • | • | • | • | • | • | • |
| Record the combination
drug/vaccine             |   | • | • | • | • | • | • | • | • | • |

\* V0 is the time for the enrollment for a booster dose.

## **1. Background and Principle**

### **1.1 Pathogen**

2019 Novel Coronavirus 2019(SARS-CoV-2) belongs to the genus  $\beta$  of coronavirus, with enveloped granules that are round or elliptic, often pleomorphic, with diameters ranging from 60 nm to 140nm. Its genetic characteristics are significantly different from those of SARS-CoV and MERS-CoV.

SARS-CoV-2 Coronaviruses belong to the genus Coronavirus in the family Coronaviridae. Coronaviruses are single-stranded RNA viruses with an envelope. They are a large group of viruses that exist widely in nature. Globally, 10% to 30% of upper respiratory tract infections are caused by HCoV-229E, HCoV-OC43, HCoV-NL63 and HCoV-HKU1, which are the second leading cause of the common cold, after rhinoviruses. Middle East Respiratory Syndrome (MERS) and Severe Acute Respiratory Syndrome (SARS), caused by coronavirus, are known to be serious infectious diseases.

The coronavirus genome encodes spike protein (S), envelope protein (E), membrane protein (M) and nucleoprotein (N) in sequence. Among them, S protein is the most important surface protein of coronavirus, which is related to the transmission ability of the virus. S protein contains two subunits: S1 and S2. S1 mainly contains receptor binding region, which is responsible for the recognition of cellular receptors. S2 contains the basic elements for the membrane fusion process. In the previous development of SARS and MERS vaccines, S protein was used as the most important candidate antigen.

### **1.2 Disease and epidemiological background**

The COVID-19 is mainly characterized by fever, dry cough and fatigue. A small number of patients have symptoms such as nasal congestion, runny nose, sore throat, myalgia and diarrhea. Severe patients usually develop dyspnea and/or hypoxemia one week after onset, and in severe cases, rapid progression to acute respiratory distress syndrome, septic shock, refractory metabolic acidosis, haemorrhagic dysfunction and multiple organ failure, etc. It is worth noting that the course of the disease in the severe and critical patients may be moderate to low fever, or even no obvious fever. Some children and newborns showed atypical symptoms, such as diarrhea, vomiting and other digestive tract symptoms, or only mental weakness and shortness of breath.

At present, the source of infection is mainly patients infected by SARS-CoV-2. An asymptomatic infected person may also be a source of infection. The main route of transmission is by respiratory droplets and close contact is the main route of transmission. Exposure to high concentrations of aerosols in a relatively closed environment for a long period of time has the potential for aerosol transmission. SARS-CoV-2 can be isolated from feces and urine, and attention should be paid to the aerosol or contact transmission caused by feces and urine to environmental pollution. The population is generally susceptible.

### **1.3 Basis of the study**

Currently, there are five major platforms of COVID-19 vaccine worldwide, namely, inactivated vaccine, viral vectored vaccine, live attenuated vaccine, recombinant protein vaccine and nucleic acid vaccine. The inactivated COVID-19 vaccines are developed by China Biotechnology Technology Co., Ltd. and Sinovac Life Science Co., Ltd. and Recombinant adenovirus type 5 vectored (**Ad5-nCoV**) jointly developed by Military Academy of Military Medical Institute and CanSino Biologics Inc have got conditional approval on the market in China. In addition, protein-subunit-based COVID-19 vaccine (ZF2001), jointly developed by the Institute of Microbiology, Chinese Academy of Sciences and Anhui Zhifei Longcom Biopharmaceutical has been granted emergency use authorization from National Medical Products Administration on March 2021.

Up to now, preliminary results from phase 3 clinical trials showed that the short-term protection rates of inactive vaccine developed by Sinovac and Ad5 vectored vaccine developed by CanSino were 50.4% and 65.7%, respectively. Although two vaccines met the requirement of WHO for the minimum protection rate of 50%, the protection rates were moderate. Comparing to the 95% protection rate of mRNA vaccine against COVID-19 developed by Moderna and Pfizer/ Biontech, the inactive vaccine and Ad5 vectored vaccine seemed to have a lower efficacy.

In order to induce a robust immune response, Russia deployed a heterologous prime-boost schedule using Ad26 and Ad5 vectored COVID-19 vaccine, which has shown 91.6% efficacy against COVID-19. The United Kingdom has also announced a heterologous prime-boost immunization study of adenovirus vectored COVID-19 vaccine and mRNA vaccine, with a view to optimizing the immunization program of the existing COVID-19 vaccine and achieving better protective effect in a

short time.

Among different vaccine modalities, heterologous strategies have shown to enhance humoral and cellular responses in several animal models. However, there is lack of regulatory guidance on heterologous (cross-platform) prime-boost immunization. In theory, the types and characteristics of the immune response induced by Ad5 vectored vaccine and protein subunit vaccine deliver antigens through different vaccine components or vector types, and the prime-boost vaccination of the two vaccines at different time points may improve the quality of the immune response, and optimize the existing immunization strategies.

In this study, subjects who have completed a dose of Ad5 vectored COVID-19 vaccine will be enrolled again to receive a booster dose of COVID-19 recombinant protein subunit vaccine at 28 or 56 days after the prime dose, which forms a heterologous prime-boost immunization program. To evaluate the effect of immunogenicity after immunization, the subjects in each regimen will be randomly vaccinated with the booster dose of subunit vaccine(ZF2001) against COVID-19 or a commercial influenza vaccine in a ratio of 2:1. In addition, due to clinical trial (JSVCT093) with two doses of Ad5 vectored COVID-19 vaccine and the phase I / II clinical trial with three dose of recombinant protein subunit vaccine (CHO cells) in healthy adults prior to this study, their serum samples after last vaccination can be provided for parallel detection of immunogenicity data, to provide complete control data.

The clinical study protocol is formulated in accordance with the requirements of the Vaccine Administration Law, the Good Practice for Quality Management of Drug Clinical Trials (GCP), the Technical Guiding Principles for Quality Management of Vaccine Clinical Trials and the Guiding Principles for Quality Management of Vaccine Clinical Trials (Trial).

## **2. Research Purposes**

To evaluate safety and immunogenicity of a heterologous prime-boost immunization of recombinant COVID-19 Vaccine (Ad5 Vector) and RBD-based protein subunit vaccine (CHO) against COVID-19 in Chinese healthy adults.

### **3. Trial Design**

#### **3.1 Design procedures**

This study is a single center, randomized, observer blind, placebo-controlled heterologous prime-boost immunization clinical trial, with “0-28 days” and “0-56 days” immunization regimens. The subjects are divided into two age groups, i.e. 18-59 years and 60 years and above.

Stage 1: According to the "0-28 days" regimen, sixty eligible subjects (30 in each age group) meeting the protocol requirements will be randomly assigned in a 2:1 ratio to receive a RBD-based protein subunit vaccine (CHO) or placebo (influenza vaccine).

Stage 2: According to the "0-56 days" regimen, sixty eligible subjects (30 in each age group) meeting the protocol requirements will be randomly assigned in a 2:1 ratio to receive a RBD-based protein subunit vaccine (CHO) or placebo (influenza vaccine).

Stage 3: For 0-28 days regimen and 0-56 days regimen, all participants receive a boost vaccination with ZF2001 at 4 months after the 1st boost dose.

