#### **3.2 Study Endpoints**

##### **3.2.1 Primary endpoints:**

- Incidence of solicited adverse events within 7 days after each booster vaccination.
- GMT of neutralizing antibodies against live SARS-CoV-2 virus at day 14 after each booster vaccination.

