##### **3.2.2 Secondary endpoints:**

###### **1. Safety endpoints**

- Incidence of adverse reactions within 28 days after each booster dose;
- Incidence of unsolicited AE within 28 days after each booster dose;
- Incidence of serious adverse events(SAE) from the 1st booster dose to the month 6 after the 2nd booster vaccination

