### 3.4 Sample size calculation

Sample size:

Hypothesis: GMT of vaccine group is superior to that in the control group at day 28 after the booster vaccination.

The baseline GMT level before the booster immunization is expected to be about 1:20 ( $\log_{10}X=1.3$ ) after one dose of prime vaccination with Ad5 vectored COVID-19 vaccine. After the booster dose, GMT level in the vaccine group is estimated to reach 1:60 ( $\log_{10}X=1.78$ ), while the control group remains 1:20. Assume that the Standard Deviation is about 4 ( $\log_{10}X=0.6$ ), and the allocation ratio for the vaccine group and placebo group is 2:1, then the minimal sample size to provide 80% power calculated is 40 and 20, respectively.

In each regimen group, subjects are stratified to two sub-age groups: 18-59 years and 60 years or above.

Table 3. Sample size of each immunization regimen

| regimen   | Sub-age group     | sample size                |                       |
|-----------|-------------------|----------------------------|-----------------------|
|           |                   | Experimental vaccine group | Placebo control group |
| 0-28 days | 18-59 years       | 20                         | 10                    |
|           | 60 years or above | 20                         | 10                    |
| 0-56 days | 18-59 ages        | 20                         | 10                    |
|           | 60 years or above | 20                         | 10                    |
| Total     | —                 | 80                         | 40                    |

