### **5.8.3 Data statistics method**

During statistical analysis, first, the number of completed cases and drop-out cases should be checked. Then demographic and baseline characteristics of each group at enrollment should be analyzed to investigate intergroup comparability. Efficacy evaluation of vaccine includes the determination of evaluation indicators and intergroup comparison of efficacy. Safety evaluation includes the statistics of clinical ARs/AEs.

Participant elimination criteria: participants don't meet the inclusion criteria; data and information after vaccination are not followed up; information and data after randomization are seriously missing; participants meet exclusion criteria but are not withdrawn; participants receive wrong vaccination or

incorrect dose.

Safety analysis in this trial mainly includes descriptive analysis of the incidence of ARs/AEs.  $\chi^2$  test may be carried out for intergroup comparison, and Fisher's exact test may be performed if necessary. After immunization, the number of case-times and person-times of local AEs in the high-dose group will be calculated (with conventional calculation method). The number of person-times will be calculated based on the highest severity in both arms, and the number of case-times will be calculated based on the cumulative local AEs actually occurring at the vaccination site. Logarithmic transformation is required for analysis of immunogenicity indicator of antibody level which should be expressed as GMT, standard deviation, median, maximum and minimum and 95% confidence interval. Classification indicators will be compared between groups. Antibody seroconversion rate will be analyzed by  $\chi^2$  test and Fisher's exact test may be used if necessary. Study data at different time points will be analyzed with statistical analysis for repeated measurement data.

SAS 9.4 is adopted for all statistical analyses with two-sided test. The P value is directly calculated while carrying out Fisher's exact test when test statistics and corresponding P values are given, and in case of  $P \leq 0.05$ , the difference is statistically significant.

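### From V4 on every participant has received ZF2001, so the second-booster part of the primary GMT endpoint has no placebo contrast and no hypothesis, and the single SAE window mixes controlled with uncontrolled follow-up

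*Protocol*

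**What the plan says.** Within each regimen, participants are randomised 2:1 to ZF2001 or influenza vaccine at the first booster only (Protocol 3.1 and 3.3). At V4, in both regimens, "all participants receive a boost vaccination with ZF2001 at 4 months after the 1st boost dose". The design is called placebo-controlled without limit to the period before V4.

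The primary immunogenicity endpoint in 3.2.1 is "GMT of neutralizing antibodies against live SARS-CoV-2 virus at day 14 after each booster vaccination", which covers V2 and V6. The primary solicited-AE endpoint is likewise defined after each booster.

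Section 3.4 states one hypothesis: superiority of the vaccine group at day 28 after a single booster. The vaccine group is expected at 1:60, "while the control group remains 1:20", and "then the minimal sample size to provide 80% power calculated is 40 and 20, respectively".

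The secondary SAE endpoint in 3.2.2 is "Incidence of serious adverse events(SAE) from the" first booster to month 6 after the second, with no break at V4.

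Sections 3.4 and 5.8 give no hypothesis, expected titre or comparison for the second booster.

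**The concern.** A primary endpoint should have a stated question. For the second-booster GMT the only question on offer is the superiority statement in 3.4, whose control premise fails once controls have had ZF2001 themselves. What remains at V6 is a randomised comparison of two ZF2001 doses with influenza vaccine followed by one ZF2001 dose. That is a legitimate question, but it is not ZF2001 versus placebo. Because the placebo-controlled label is unqualified, a V6 contrast in either direction could be reported as placebo-controlled evidence.

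For safety, a single SAE incidence per arm over the whole window counts events during ZF2001 exposure under the control arm and so dilutes any ZF2001-versus-influenza difference. Solicited AEs after the second booster have no unexposed concurrent group at all.

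**Working it through.** **Inputs.** From 3.4: difference 1.78 − 1.30 = 0.48 log10, SD 0.6 log10, 2:1 allocation, 80% power. Section 3.4 states no alpha. Section 5.8.3 gives the general rule: "SAS 9.4 is adopted for all statistical analyses with two-sided test", and at P ≤ 0.05 "the difference is statistically significant". Visit days are from Tables 1 and 2.

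**1. Reproducing the plan's figure (first booster).**
- Normal approximation: n(control) = (1.960 + 0.842)² × 0.6² × 1.5 / 0.48² = 18.4, so 19 control and 38 vaccine.
- Noncentral t: 20 and 40, exactly as stated.
- Power at 40/20: 83% (normal) or 82% (t).
- V2 and V3 both precede V4, so the control premise holds there and the calculation stands.

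**2. The same sample at V6.** The standard error of the log10 GMT difference is 0.6 × √(1/40 + 1/20) = 0.164. The protocol gives no V6 titres, so the ratios below are assumed. Power is two-sided at 0.05, noncentral t with 58 df.

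| V6 GMT ratio | log10 difference | difference / SE | power |
|---|---|---|---|
| 3-fold (planned first-booster ratio) | 0.477 | 2.90 | 81% |
| 2-fold (assumed) | 0.301 | 1.83 | 44% |
| 1.5-fold (assumed) | 0.176 | 1.07 | 18% |

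The difference detectable with 80% power is 0.468 log10, and 10^0.468 = 2.94-fold. The normal approximation gives 0.460, or 2.89-fold. For the sample to be adequate at V6, the arm with two ZF2001 doses would have to exceed the arm with one by nearly the ratio that 3.4 expects of ZF2001 over no COVID-19 booster.

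**3. Time point.** The powered hypothesis in 3.4 is at day 28 after the booster, while the primary GMT in 3.2.1 is at day 14. Even for the first booster, the power statement and the primary endpoint name different visits.

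**4. SAE window in the control arm.**
- 0-28 regimen: V0 day 28, V4 day 150, V8 day 330. After ZF2001: 330 − 150 = 180 days. Total: 330 − 28 = 302 days. 180/302 = 59.6%.
- 0-56 regimen: V0 day 56, V4 day 180, V8 day 360. After ZF2001: 360 − 180 = 180 days. Total: 360 − 56 = 304 days. 180/304 = 59.2%.

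The protocol gives no SAE rate, so the amount of dilution cannot be computed.

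**The case against.** The strongest reply is that nothing planned is broken. Section 3.4 concerns one booster, its arithmetic reproduces, and the visits it covers come before V4. The Document History for version 1.3 gives the purpose of the second dose as raising responses further, which is not a vaccine-versus-control question. Section 5.8.3 treats safety as mainly descriptive, with between-group tests optional. Splitting an SAE table at V4 could be left to the statistical analysis plan, which 5.7.4 mentions and which is not at hand. Most of this stands, and it confines the point to V4 onward. It does not explain why 3.2.1 gives the V6 GMT primary status while 3.4 offers no purpose for it.

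A reader might infer more than the protocol supports:

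- **The sample size is invalid.** It is not. It was never extended to V6.
- **Familywise error reaches 18.5%.** That is 1 − 0.95⁴, for two regimens at two time points. It presumes four confirmatory tests, all nulls true and independence. The protocol states no V6 test, and V2 and V6 come from the same participants.
- **A null V6 result means a failed primary endpoint.** No pass/fail rule is given for V6.
- **The repeated-measures analysis mixes the two contrasts.** The text says only "Study data at different time points will be analyzed with statistical analysis for repeated measurement data". A model with group-by-visit terms keeps the visits apart, and the terms are not specified.
- **The double-dose arm must reach 1:176.** That is 60 × 2.94 and assumes controls reach 1:60 at V6, which the protocol does not say. The 2.94-fold ratio needs no control titre.

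**Conclusion.** The point holds for V4 onward and should be fixed, but it does not undermine the first-booster comparison. The V6 part of the primary GMT endpoint has no placebo contrast, hypothesis or size of its own. The 40/20 sample detects about a 2.9-fold difference there, with about 44% power at 2-fold and 18% at 1.5-fold. These figures assume that SD 0.6 carries over to V6, that all 60 participants per regimen contribute, and that the test is two-sided at 0.05. About 60% of control-arm SAE follow-up is after ZF2001. The direction of the dilution follows from the design, but its size is unknown. Giving every participant ZF2001 is not in question here; how the resulting data are labelled and compared is.

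**What to change.** (a) In 3.2.1 and 3.4, limit the placebo-superiority hypothesis and the 80% power statement to the first booster, and reconcile its time point (day 14 in 3.2.1, day 28 in 3.4). Report second-booster GMT by sequence, ZF2001-ZF2001 versus influenza-ZF2001, as a GMT ratio with 95% CI, and call it descriptive.

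(b) Report SAEs separately for V0 to before V4 (randomised ZF2001 versus influenza vaccine) and from V4 to V8 (by sequence, all ZF2001-exposed). State that solicited AEs after the second booster have no unexposed control.

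The cost is wording in the protocol and analysis plan, with no change to vaccination, visits or sampling. The second-booster GMT loses confirmatory status. The change must be disclosed as made after first-booster day-14 titres were known, since the Document History gives those titres as the reason for version 1.3.
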